### Blinding

Due to the study design, the attending anaesthesiologist can’t be blinded to the study intervention. Therefore, double blinding will not be feasible. However, the patient is blinded to his study group and postoperative data collection and statistical analysis will be performed by investigators blinded to the group allocation of each patient. Since the attending physicians is unblinded to the study intervention, no emergency unblinding strategy has been developed.

### Data collection, management and analysis

All data will be collected in real-time by the clinical research team of the participating centres using a case report form. The variables to be collected are as follows:Demographics (age, gender, ASA score, height, weight, BMI).Comorbidities: Charlson comorbidities score and preoperative score to predict postoperative mortality (POSPOM).Surgical risk (ACS NSQIP surgical risk evaluation) and surgical procedure.Perioperative:◦ Haemodynamic (continuous): mean, systolic and diastolic blood pressure, heart rate, cardiac output, stroke volume, stroke volume variation and ScvO_2_ for the patients in the experimental group.◦ Respiratory (every 30 min): tidal volume, respiratory rate, FiO_2_, positive end-expiratory pressure (PEEP).◦ Neurologic (every 30 min): bispectral index (BIS), suppression ration (SR).At the end of surgery: total volume of fluids administered (crystalloids and blood products), type and total amount of anaesthesia drugs used, use of an epidural analgesic.In the PACU: arterial and venous blood gas analysis, LUS.Postoperative (daily): type and severity of postoperative complications until day 5 postoperative. CCI score calculation on day 5.At day 15 postoperative: collection of postoperative complications between day 5 and day 15 and CCI score calculation on day 15.At day 30 postoperative: collection of postoperative complications between day 15 and day 30 and CCI score calculation on day 30.

Data entry will be performed using REDCap software. Data analysis will be performed by a statistician from the clinical research team, using SPSS software (v 17.0, IBM, USA).

Table 1 shows the schedule of enrolment, intervention and assessment during the study period.

**Table 1 Tab1:** Schedule of enrolment, interventions and assessments

	**Study period**							
	**Enrolment**	**Allocation**	**Post-allocation**					**Close-out**
**Timepoint**	**Pre-anaesthesia consultation**	**Surgery day**	***t***_***1***_ *During surgery*	***t***_***2***_ *PACU*	***t***_***3***_ *D1 to D5 postop*	***t***_***4***_ *D15 postop*	***t***_***4***_ *D30 postop*	**D30 postop**
**Enrolment:**								
Eligibility screen	X							
Informed consent	X							
Allocation		X						
**Interventions:**								
Control group: standard care			X					
Intervention group: ScvO_2_-guided GDT			X					
**Assessments:**								
Demographics, comorbidities, surgical risk		X						
Haemodynamic, respiratory and neurologic variables Total fluid administration			X					
Arterial and venous blood gas analysis, LUS				X				
Postoperative complications, CCI					X	X	X	
Close-out form								X

Abbreviations: *PACU* post-anaesthesia care unit, *D* day, *GDT* goal-directed therapy, *LUS* lung ultrasound score, *CCI* Comprehensive Complication Index

### Statistical methods

Statistical analysis will start only after the database has been validated (all queries answered, database coherence controlled). The statistical analysis will be blinded (no explicit identification of groups). The methodology and statistical analysis will be performed in accordance with the CONSORT statement [13]. The population analysis will be performed according to the intention-to-treat (ITT) principle. A secondary, per-protocol population analysis will be performed if needed. If present, missing data will be handled via multiple imputation by chained equations. Categorical variables will be reported as count (%) and continuous variables as mean (± standard deviation (SD)) or median (25th–75th quartile range). The presence of a normal distribution will be verified using the Kolmogorov-Smirnoff test. We will use the *t*-test to assess differences between parametric continuous variables, the Mann–Whitney test for non-parametric variables, the *χ*^2^ test for categorical variables and the Fisher exact test for 2 × 2 tables. No correction for multiple testing will be done. A two-sided *p* < 0.05 will be considered statistically significant. Stopping of the trial could also be based on interim data analysis if clearly one treatment is better than the other, but no interim analysis is planned.

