### Outcomes

The primary outcome will be the Comprehensive Complication Index (CCI) on day five after surgery [9]. CCI is a validated score for postoperative morbidity, ranging from 0 (no complication) to 100 (death). This score is based on the Clavien-Dindo classification of postoperative complications, and it weighs the severity of the complications by the resources needed to treat them [10]. CCI offers a sensitive endpoint and is particularly suitable for randomised controlled trials [11].

Regarding secondary outcomes, our hypothesis is that our experimental strategy will reduce the quantity of fluid administered during surgery. Therefore, the secondary outcomes will be the total amount of fluid administered perioperatively and the lung ultrasound score (LUS). LUS is a simple, fast and reproducible measure to assess the potential harm of excessive fluid administration [12]. To assess long-term outcomes, the CCI will be measured at days 15 and 30.

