### Sample size

A sample size calculation was made from published data [9, 11]. In order to show a 10% difference in CCI between groups on day five after surgery, with a 0.9 power and a 0.05 alpha risk, 100 patients were needed per group. Considering a potential 10% loss to follow-up, we included 220 patients (110 patients per group). We chose a 10% difference in CCI because this represents a clinically significant decrease in postoperative complications (one grade on the Clavien-Dindo classification).

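### A normality pre-test on the trial data picks the primary test, so neither the test nor the effect measure for day-5 CCI is fixed in advance

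*Protocol article*

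**What the plan says.** Outcomes section: "The primary outcome will be the Comprehensive Complication Index (CCI) on day five after surgery". The scale is described as "ranging from 0 (no complication) to 100 (death"), so every patient without a complication has the same value, 0.

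Statistical methods section: "The presence of a normal distribution will be verified using the Kolmogorov-Smirnoff test". Variables that pass go to a t-test; for those that do not, the plan is "the Mann–Whitney test for non-parametric variables". The rule covers continuous variables in general and makes no exception for the primary outcome. No effect measure is named. If values are missing, "missing data will be handled via multiple imputation by chained equations". The test is two-sided at 0.05, and the analysis is done without group identity.

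Sample size section: "A sample size calculation was made from published data". The target is worded "In order to show a 10% difference in CCI between groups on day five after surgery", and "with a 0.9 power and a 0.05 alpha risk, 100 patients were needed per group". The section does not give an SD, does not say whether the 10% means points or a proportion, and names neither a mean nor a test. It describes the difference as clinically significant.

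Allocation section: randomisation is stratified by centre.

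**The concern.** The t-test compares means. Mann–Whitney asks whether values in one arm tend to be larger than in the other. On a skewed index with a block of zeros these questions can have different answers, and here a preliminary test on the trial data chooses which one is asked.

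Two things are at stake. First, the trial is justified by a difference on the CCI scale that is called clinically significant. If the primary result is a Mann–Whitney p-value, there is no difference in CCI points and no confidence interval to compare with that target. Second, the stated power of 0.9 belongs to whichever comparison was used for sizing, and it need not hold for the test that is finally run.

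This is not a detail left to an analysis plan that is not shown. The article states a rule, and the rule makes the choice depend on the data.

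**Working it through.** **1. The plan's own figure.** Inputs from the Sample size and Statistical methods sections: 100 per group, power 0.90, two-sided alpha 0.05. No SD is given, so 100 cannot be reproduced, only inverted. For two means, n = 2·SD²·(1.960 + 1.282)²/d², hence SD = d/[3.242·√(2/100)].
- d = 10 points: SD = 10/(3.242 × 0.1414) = 21.8.
- d = 10% of a control mean of 20 to 40 (assumed), that is 2 to 4 points: SD = 4.4 to 8.7.

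The second SD is very small for a 0–100 index with a block of zeros, so 10 points is the more plausible reading. It remains an inference.

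**2. When does the pre-test force Mann–Whitney?** If a share p0 of patients sits at exactly 0, the empirical distribution jumps by p0 there. A fitted normal curve is continuous, so the Kolmogorov–Smirnov distance is at least p0/2. Rejection at 5% is certain once p0/2 exceeds the critical value: 0.886/√n with the Lilliefors correction, 1.358/√n without.

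| Patients tested | Lilliefors: p0 | Uncorrected: p0 |
|---|---|---|
| 100 | 2 × 0.0886 = 18% | 2 × 0.1358 = 27% |
| 220 | 2 × 0.0597 = 12% | 2 × 0.0916 = 18% |

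The article does not say which version is meant, or whether normality is checked by arm or overall. In simulation (zeros plus a scaled beta, samples of 100 and 200) with 30–60% zeros, Lilliefors rejected in 99.8–100% of samples and the uncorrected test in 83–100%. With 10% zeros, rejection ranged from 10% to 100% depending on n and version.

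**3. Do the two tests have the same power?** Simulated trials with 100 per group and a true mean difference of 10 points; all distributions are assumed.

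| Assumed control distribution | Source of the 10 points | t-test | Mann–Whitney |
|---|---|---|---|
| 35% zeros, gamma mean 34, CV 0.55 | fewer complications | 0.92 | 0.97 |
| same | lower severity | 0.98 | 0.82 |
| 55% zeros, gamma mean 40, CV 0.5 | fewer complications | 0.90 | 0.97 |
| same | lower severity | 0.98 | 0.52 |
| 35% zeros, scaled beta mean 45 | fewer complications | 0.74 | 0.81 |
| same | lower severity | 0.82 | 0.61 |

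The last two rows have a control SD of about 27, above the implied 21.8, which lowers the t-test's power too. The fourth row is extreme: the control mean is 0.45 × 40 = 18, and taking off 10 points without preventing any complication cuts mean severity from 40 to 40 − 10/0.45 = 17.8.

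**4. Do they answer the same question?** With both means at 20 but 50% zeros in one arm and 35% in the other (scaled beta), Mann–Whitney rejected in 13.7% of trials and the Welch t-test in 5.1%. The arms do differ here, in shape. This shows a difference in target, not a false-positive rate.

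**5. Type I error of the two-stage rule.** With identical distributions in both arms, 100 per group and 5–55% zeros, the two-stage procedure rejected in 4.5–5.3% of trials.

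**6. Imputation.** Filling 10% of values by random draws, ten times per trial, gave Lilliefors verdicts that differed between imputed sets in 23% of trials at 10% zeros, and in none at 30–50% zeros. The rule does not say which verdict would count.

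**The case against.** Several objections have force.

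- **The sizing basis is not stated.** The article names no mean, SD or test, and its published sources are not at hand. A reader might infer that the trial was sized on a mean difference and that the 0.9 power belongs to a t-test. The text does not say so. This stands; what remains is that the target is a size on the CCI scale, which a rank p-value does not estimate.
- **Imputation.** A reader might infer that Mann–Whitney cannot be combined with multiple imputation. That is too strong. The Mann–Whitney probability with its standard error, or the z-statistics, can be pooled; only a bare p-value cannot go through Rubin's rules. Imputation applies only if data are missing, and pooling details may sit in a document not shown.
- **Error rate.** A reader might infer an inflated false-positive rate. Step 5 shows none, and the blinded analysis limits any steering of the test choice.
- **If the pre-test nearly always rejects, the choice is in effect fixed.** This is fair when zeros are common. But the share of zeros is unknown in this high-risk population, and with few zeros the outcome is unpredictable. With many zeros, the primary result is a rank p-value with no stated effect measure. The primary analysis is poorly specified either way.
- **A rank test is legitimate for a bounded, skewed index.** It is, and it is the more powerful choice when the effect is mainly fewer complications, which fits the stated hypothesis at least as well as lower severity. The problem is leaving the choice to the data, not the use of ranks.

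**Conclusion.** The point holds as a cheap improvement. The stated rule lets trial data choose the primary test and, with it, the effect measure for day-5 CCI. Mann–Whitney is the likely result if roughly 12–27% or more of patients score 0; that they do is an assumption, because the documents give no share. In that case the primary p-value could not be read against the 10% target, and the power could lie above or below that of a t-test: 0.52 to 0.97 against 0.74 to 0.98 in the scenarios shown, all with assumed distributions. The 10-point reading and the SD of 21.8 are inferred from the 100 per group. The documents support neither an invalid error rate nor an unworkable imputation plan.

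**What to change.** Drop the normality pre-test for the primary outcome and prespecify one analysis before unblinding: the difference in mean day-5 CCI, in points, with a 95% CI, from a linear model on arm adjusted for centre (the stratification factor) with robust standard errors. If data are imputed, pool the estimates by Rubin's rules. Report Mann–Whitney as a sensitivity analysis.

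The cost is a change of wording. The sample size stays: 100 per group still serves a 10-point mean difference at the implied SD of 21.8. There is a small downside: a mean is sensitive to a few deaths scored 100, and it has somewhat less power than the rank test if the effect is mainly fewer complications (0.90–0.92 against 0.97, and 0.74 against 0.81, in the scenarios above). The rank sensitivity analysis covers both.

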### Monitoring

In accordance with the Helsinki Declaration and French law, the research team will declare adverse events without delay to the study sponsor (Assistance Publique Hôpitaux de Marseille). Participation in the study will be clearly stated in the patients’ medical files. The data monitoring and the coordinating committees from the study sponsor will perform annual data-monitoring sessions for quality control and trial conduct auditions during the study period.

## Ethics and dissemination

### Research ethics approval

This study was approved by an institutional review board (Comité de Protection des Personnes SUD-EST VI) on December 9, 2019. All participants will be able to consent to the study and written consent will be obtained from all participants. Minors and patients unable to understand the study or under guardianship will not be included.

### Protocol amendments

Two amendments have been made to the original protocol. The first amendment removed the diagnosis of heart arrhythmia from the exclusion criteria, because stroke volume variation was not used in the study to assess fluid responsiveness. Due to safety concerns, the second amendment added the 250 mL fluid loading in the experimental group should the norepinephrine dose exceed more than 0.5 µg kg^−1^ min^−1^. All participating centres were notified without delay by the study sponsor of any protocol amendments. If a major deviation from the study protocol should happen, it will be documented by the investigators with a Breach Report Form.

### Consent or assent

All participants will have consented to the study. Minors and patients unable to understand the study or under guardianship will not be included.

### Confidentiality

The database will be anonymous and encrypted to ensure data safety and patient confidentiality.

### Access to data

The datasets analysed during the current study and statistical code will be available from the corresponding author, BP, on reasonable request, as is the full protocol.

### Ancillary and post-trial care

Patients enrolled in the study will be covered by indemnity for negligent harm through the standard indemnity arrangements of French national health insurance. Hôpitaux Universitaires de Marseille has insurance to cover non-negligent harm associated with the protocol.

### Dissemination policy

The authors aim to publish the present protocol in a high-impact, peer-reviewed anaesthesiology journal. The results will be published even in the event of non-significant results.

## Data Availability

The datasets analysed during the current study and statistical code will be available from the corresponding author, BP, on reasonable request, as is the full protocol.
